### Harms

The frequency and percentage (%) of serious adverse events and adverse events in the trial will be compared between the two treatments using the chi-squared test provided the expected values in the cross-tabulation are greater than 5; otherwise, Fisher’s exact test will be used. Odds ratios and 95% confidence intervals will be reported. Adjusted analyses will not be performed for any harm data. The event type, severity assessment, expectedness, and relatedness to intervention will also be summarised by offer of treatment or cohort only.

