### Sample size {14}

The sample size calculation is based on detecting a difference of 20% between the intervention group and the remaining cohort achieving a sustained return to work (1:3 allocation ratio). Assuming a cohort return to work rate as high as 10%, with a power of 80% and a 5% significance level, we will need data on 176 participants (132 control and 44 intervention) [13]. Allowing for a 20% loss to follow-up and a crude 14% inflation in the intervention group for an estimated design effect due to clustering by the case manager (assumptions here are an ICC of 0.01, smallest cluster size of 7 and largest of 16, and so a design effect of 1.14), we will aim to recruit 228 people [59]. If a 1:3 ratio allocation provides insufficient throughput for us to regularly form small groups of people for the work preparation session due to the proportion of people not accepting the intervention being high, we may switch to target overall balanced randomisation (1:2). In this case, our overall required sample size will be reduced to 190 in total, with the above inflations (with the same assumptions the estimated design effect will be 1.11 in this case) [59].

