### Adverse event reporting and harms {22}

Adverse events will be reported via case managers. Minor adverse events (e.g. a participant being distressed during a session) are logged by the case manager and reported to the trial manager. Serious adverse events related to the study or within the study setting (e.g. during a meeting between the participant and case managers) are reported immediately to the chief investigator in accordance with good clinical practice guidelines. If necessary, the adverse event is reported to the sponsor and to the Norwegian Board of Health Supervision.

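### The odds ratio is the only effect measure fixed for harms, and for rare events it can be undefined, unbounded above or too wide to use; a risk difference should be added

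*Protocol article*

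**What the plan says.** The Harms section of the protocol article plans four things:

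- Counts and percentages: "The frequency and percentage (%) of serious adverse events and adverse events in the trial" are to be given.
- A test: these "will be compared between the two treatments using the chi-squared test provided the expected values in the cross-tabulation are greater than 5", with Fisher's exact test otherwise.
- An estimate: "Odds ratios and 95% confidence intervals will be reported. Adjusted analyses will not be performed for any harm data".
- A description: event type, severity, expectedness and relatedness "will also be summarised by offer of treatment or cohort only".

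The odds ratio is the only effect measure named. The section gives no interval method, no rule for zero counts and no expected event rate. The Sample size section sets the scale of the trial: "we will aim to recruit 228 people", with a 1:3 ratio of intervention to cohort-only participants.

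**The concern.** The plan adapts the test to sparse tables but not the estimate. The condition on the chi-squared test, "provided the expected values in the cross-tabulation are greater than 5", shows that small counts are foreseen. Yet the one measure meant to convey the size of any harm behaves worst when counts are small, and the intervention arm holds only about a quarter of the participants.

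At stake is what the trial can say about serious harm. A useful safety statement bounds the excess: how many more people per hundred could be harmed by being offered the placement, given the data. When the cohort-only arm has no events, the odds ratio cannot supply an upper bound. Events in the intervention arm and none in the cohort is the pattern most suggestive of harm, so the planned measure fails where it is most needed.

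**Working it through.** **Arm sizes.** The plan's total reproduces from the Sample size section: (132 + 44 × 1.14) / 0.8 = 182.16 / 0.8 = 227.7, so 228. A straight 1:3 split of 228 is 57 v 171, used below. Carrying the inflation through by arm gives 44 × 1.14 / 0.8 = 62.7 and 132 / 0.8 = 165, so about 63 v 165. Reading the one-in-three offer in the Trial design section literally gives 76 v 152.

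**Chance of zero counts.** The event rate p is an assumption, taken as equal in both arms. With n₁ = 57 and n₀ = 171:

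- P(cohort-only arm zero) = (1 − p)^171
- P(both zero) = (1 − p)^228
- P(at least one arm zero) = (1 − p)^57 + (1 − p)^171 − (1 − p)^228

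At p = 1%: 0.564 + 0.179 − 0.101 = 0.642.

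| Assumed rate | Cohort-only arm zero (no upper limit, or undefined) | Both zero (undefined) | At least one arm zero |
|---|---|---|---|
| 0.5% | 42% | 32% | 86% |
| 1% | 18% | 10% | 64% |
| 2% | 3% | 1% | 34% |
| 3% | 0.5% | 0.1% | 18% |
| 5% | <0.1% | <0.1% | 5% |

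The last column is not sensitive to the split. At 0.5%, 1%, 2% and 3% it is 85%, 62%, 31% and 15% with 63 v 165, and 83%, 58%, 25% and 11% with 76 v 152.

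**What the odds ratio gives.** The exact conditional interval is the natural partner of Fisher's test.

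- *0/57 v 2/171.* The estimate is 0. The upper limit ψ solves C(171,2) / [C(171,2) + 57 × 171 ψ + C(57,2) ψ²] = 0.025, that is 14535 / (14535 + 9747ψ + 1596ψ²) = 0.025, so ψ = 16.0. The interval is 0 to 16.0.
- *3/57 v 0/171.* The estimate is infinite. The lower limit solves 29260ψ³ / (818805 + 828495ψ + 272916ψ² + 29260ψ³) = 0.025, so ψ = 1.26. There is no upper limit.
- *0/57 v 0/171.* Undefined.

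**What the risk difference gives.** Newcombe's interval combines the Wilson limits (l, u) of each arm. With d = p₁ − p₀, the lower limit is d − √[(p₁ − l₁)² + (u₀ − p₀)²] and the upper limit is d + √[(u₁ − p₁)² + (p₀ − l₀)²].

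- *0/57 v 2/171.* Wilson limits are 0 to 6.31% and 0.32% to 4.16%; d = −1.17. Lower: −1.17 − √(0² + 2.99²) = −4.2. Upper: −1.17 + √(6.31² + 0.85²) = 5.2 points.
- *3/57 v 0/171.* Wilson limits are 1.81% to 14.37% and 0 to 2.20%; d = 5.26. Lower: 5.26 − √(3.46² + 2.20²) = 1.2. Upper: 5.26 + √(9.11² + 0²) = 14.4 points.
- *0/57 v 0/171.* d = 0, interval −2.2 to 6.3 points.

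It exists in all three cases and bounds the excess in each.

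**The case against.** A reader might infer that no odds ratio interval exists once an arm has no events, so that no limit on excess harm could be stated. That goes too far. The failure is general only for the usual log odds ratio (Woolf) interval, and the Harms section does not name that method. With a zero in the intervention arm alone, the exact interval has a finite upper limit. At a 1% rate with 57 v 171 this is the commonest kind of zero: (0.564 − 0.101) / 0.642 = 72% of tables with any zero. The figures for at least one zero arm therefore overstate how often the upper limit is lost; the cohort-only column is the right one for that.

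A reader might also take the words "Serious adverse events related to the study or within the study setting" in the adverse event reporting section as restricting which serious events are analysed, and so as proof that counts will be tiny. That sentence governs immediate notification to the chief investigator. It does not define the analysis set, and the planned summary of relatedness suggests that unrelated events are also counted.

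Three further points are fair. The planned counts and percentages let anyone calculate a risk difference. Odds ratios for binary harms are conventional. The interval method and zero-count rule may stand in the analysis plan, which the article says is finalised and which is not shown, so their absence here is not a fault.

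What remains is the choice the article does make. It fixes a single effect measure, and no interval method gives it a finite upper limit that rests on the data when the cohort-only arm has zero events. Adding a half to each cell for 3/57 v 0/171 gives 22.0 with limits of 1.1 to 433, which is no more use. Even the finite exact limit of 16.0 says little, where the risk difference excludes an excess above 5.2 points. The reader should not have to derive the trial's safety estimate.

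**Conclusion.** The point holds as a limited one. For rare events the planned odds ratio may be undefined, unbounded above or too wide to inform, and a risk difference avoids all three. The upper limit is lost with a chance of about 42%, 18% and 3% at event rates of 0.5%, 1% and 2%. At least one arm is empty with a chance of 86%, 64% and 34%. By a 5% rate the latter is about 5%, so common adverse events are little affected.

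These figures rest on an assumed event rate, on equal risk in both arms and on 57 v 171 participants contributing. Equal recording is a further assumption. The article routes adverse events through case managers, whom only intervention participants have, although Table 1 also lists case report forms at each follow-up. If cohort-only events are recorded less fully, zero counts in that arm become more likely than shown.

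The documents do not show that the harms analysis is invalid or that excess harm cannot be bounded. This is a cheap improvement.

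**What to change.** In the Harms section, and in the matching part of the analysis plan:

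1. Add the risk difference in the proportion of participants with at least one event, with a Newcombe or Miettinen-Nurminen 95% interval, for both adverse and serious adverse events.
2. Keep the odds ratio. State that an exact interval is used when counts are sparse, and that it is marked not estimable when both arms have zero events.
3. Keep the chi-squared and Fisher rule as it stands.

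The cost is a sentence or two of text and about a line of code, with no new data. The one small drawback is that two effect measures are shown. The gain is a harm estimate that is available for every table and lies on the same absolute scale as the 20-point difference used to size the trial.

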### Methods in analysis to handle protocol non-adherence and any statistical methods to handle missing data {20c}

The levels and patterns of non-responders at each follow-up time point will be monitored regularly. The levels and patterns of missingness in the primary outcome will first be assessed with the aim of determining the type of missingness (e.g. missing at random, not missing at random). If appropriate and required, as an additional sensitivity analysis, imputation techniques will be used to impute data and estimate the treatment effect.

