### Data collection and management

#### Plans for assessment and collection of outcomes {18a}

The planned time points and methods for outcome data collection are summarised in Table 1, with detailed information regarding primary and secondary outcome measures provided in SPIRIT item 12. Participants will be offered to complete self-reported measures in English or Norwegian (based on the preferred language as stated when providing informed consent) and on paper (by postage) or in a digital format (by email) using Nettskjema. If the measures are completed using Nettskjema, we will receive complete data as questionnaire items are mandatory. Measures conducted on paper will be entered independently by two research team members. For our primary outcome of sustained return to work, we plan to use registry data from NAV, although we could use our own questionnaire data, in the case of missing registry data. For details of care received and services used, we will use registry data. The process evaluation will utilise a mix of data (see SPIRIT items 12 and 19) collected from the questionnaires, expression of interest forms (with consent), and registry data in addition to field notes, qualitative interviews with participants, case managers, placement managers, and diary records.

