### Statistical methods

#### Statistical methods for primary and secondary outcomes {20a}

A detailed statistical analysis plan has been finalised and agreed prior to analysis by the research team. We will report all participant flow in line with the CONSORT guideline extension for reporting RCTs conducted using cohorts and routinely collected data showing withdrawal and loss to follow-up [15]. Analyses will be conducted within TSD using Stata v17 or above (Stata Corporation, College Station, TX). Participant characteristics and outcomes will be summarised as mean and standard deviation for normally distributed continuous data or with median and ranges for data with skewed distributions or counts and percentage for categorical data. The primary analysis approach will be ‘intention-to-treat’. To account for the trial design featuring clustering in the intervention arm, generalised linear (GLM) mixed effects models will be used to estimate the between-group differences for both primary and secondary continuous outcomes, adjusting for age, gender, and duration of pain, with a random intercept for case manager. For example, we will analyse the between-group differences in sustained return to work (a binary outcome) using a generalised mixed-effect model with logit link function, the above covariates, and fitting a random effect in case manager allocation.

Secondary outcomes will also be analysed using generalised mixed models, using link functions appropriate to the outcome (e.g. where outcomes are continuous, we will use a canonical link function). In all cases, we will adjust for the same covariates (i.e. age, gender, and duration of pain). The adjusted treatment effect estimates (mean difference) between the groups will be presented as point estimates within a 95% confidence interval. Our outcome measures are largely independent and no correction for multiple testing will be done. *P*-values < 0.05 will be considered statistically significant. All tests will be two-sided.

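### Section {20c} aims to tell missing at random from not at random using observed data, which cannot be done, and commits to no analysis under departures from missing at random

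*Protocol article*

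**What the plan says.** Section {20c} of the protocol article has three steps. Non-response is monitored at each follow-up. Then "The levels and patterns of missingness in the primary outcome will first be assessed", and this is done "with the aim of determining the type of missingness (e.g. missing at random, not missing at random". Finally: "If appropriate and required, as an additional sensitivity analysis, imputation techniques will be used to impute data and estimate the treatment effect". The section names no imputation method, no assumption behind it, no explicit trigger, and no analysis for the case where data are not missing at random.

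Other sections that bear on this:

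- Section {20a} gives the primary analysis: intention-to-treat, by a logit mixed model adjusted for age, gender and pain duration, with a random intercept for case manager. It is not made conditional on the missingness review. The same section says that a detailed analysis plan has been finalised.
- Sections {12} and {18a} take the primary outcome from the national labour and welfare registry. Self-report is the fallback: "although we could use our own questionnaire data, in the case of missing registry data".
- Section {14} sizes the trial with this margin: "Allowing for a 20% loss to follow-up".
- Section {11b} stops further data collection once a participant withdraws.
- The section on adherence monitoring has the process evaluation record how many drop out and why.

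**The concern.** Missing at random and not missing at random differ in one respect: whether, given everything observed, the chance of being missing still depends on the value that was not seen. Levels, patterns and baseline predictors of missingness can show that data are not missing completely at random, and they can help to build a missing-at-random model. They cannot settle the remaining question, because the values that would settle it are the ones not there. The stated aim is therefore unachievable, and no added detail in an analysis plan could make it achievable.

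This matters because the review comes first and the decision on imputation follows it. The section offers no other criterion for that decision. In this trial, finding or not finding work is itself a plausible reason to stop responding. Retention support also differs by arm: under section {18b}, case managers help to keep intervention participants in the study, and only that group has placement travel reimbursed. A robustness check should not turn on a diagnosis that the data cannot supply.

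**Working it through.** **Inputs.** From section {14}: 10% sustained return to work in the cohort, power 80%, significance level 5%, 132 + 44 = 176 evaluable participants, 20% loss, design effect 1.14, 228 recruited. The effect size is "detecting a difference of 20% between the intervention group and the remaining cohort achieving a sustained return to work (1:3 allocation ratio", so 30% in the intervention group. Section {20a} gives two-sided tests. The rates among missing participants below are assumptions.

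**Step 1: reproduce the plan's own figure.** With 30% v 10%, 1:3 allocation and continuity correction, the two-proportion formula gives 44 + 132 = 176 (38 + 114 = 152 without the correction). Inflation: (132 + 44 × 1.14) / (1 − 0.20) = 182.16 / 0.80 = 227.7, rounded up to 228. The 20% is therefore a real planning input.

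**Step 2: what the data do not determine.** In each arm, with missing share m:

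overall rate = (1 − m) × observed rate + m × rate among the missing.

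The last rate does not enter the likelihood of the observed data.

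**Step 3: put the numbers in.** With m = 0.20 in both arms and 30% v 10% observed, the observed parts are 0.8 × 0.30 = 0.24 and 0.8 × 0.10 = 0.08.

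| Assumed rate among missing (intervention / control) | Overall difference |
|---|---|
| 30% / 10% (same as observed) | 0.30 − 0.10 = 0.20 |
| 0% / 0% (missing = not returned) | 0.24 − 0.08 = 0.16 |
| 0% / 10% | 0.24 − 0.10 = 0.14 |
| 0% / 20% | 0.24 − 0.12 = 0.12 |
| 0% / 30% | 0.24 − 0.14 = 0.10 |
| 0% / 100% (lower bound) | 0.24 − 0.28 = −0.04 |
| 100% / 0% (upper bound) | 0.44 − 0.08 = +0.36 |

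Every row has the same observed data and the same missingness pattern. No review of levels or patterns can choose between the rows.

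**Step 4: dependence on how much is missing.** The bounds are (1 − m) × 0.20 ± m.

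- m = 0.10: 0.18 ± 0.10, that is +0.08 to +0.28; missing = not returned gives 0.18.
- m = 0.05: 0.19 ± 0.05, that is +0.14 to +0.24.
- The lower bound reaches zero at m = 0.20 / 1.20, about 17%.

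These are point estimates without sampling error.

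**The case against.** The strongest reply is that this is one loosely worded aim attached to an additional sensitivity analysis. Much of it stands, and it rules out several stronger readings that a reader might infer.

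- **Imputation will be run only if the data are found to be missing at random.** The text does not say so. Its condition could also mean that enough data are missing to matter, which is observable. The link to the classification comes from the order of the sentences and the absence of another criterion.
- **The imputation assumes missing at random.** No assumption is named, and the section explicitly mentions the other mechanism. What can be said is that no departure analysis is committed to.
- **The main result rests on the classification.** It does not: the model in section {20a} is specified unconditionally.
- **The choice will be made post hoc.** Section {17a} leaves the statistician unblinded under the planned allocation, but the analysis plan is not at hand and may fix the choice in advance.
- **A fifth of primary outcomes will be missing.** The 20% is a sample-size allowance, not a forecast for a registry outcome, and the extreme bounds need all missing participants in one arm to succeed and all in the other to fail.

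It is also fair that recorded drop-out reasons, and a second outcome source where one is missing, make some mechanisms more or less plausible. They still do not identify the mechanism for people with neither source. Withdrawal under section {11b} means that such people are likely to exist.

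The reply does not rescue the stated aim. Leaving detail to the analysis plan is normal, but an aim that cannot be met is an error in the protocol itself.

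**Conclusion.** The point holds as a minor correction. Section {20c} sets out to determine something that observed data cannot determine. That determination is no proper guide to whether the only named missing-data sensitivity analysis is run, and the section commits to nothing under departures from missing at random.

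The possible effect runs from negligible, if registry linkage is nearly complete, to material at the protocol's own allowance. At 20% missing in both arms, an observed 20-point difference becomes 16 if all missing count as not returned, and 14 to 10 under moderate arm-specific departures. The outer limits are −4 and +36. Below about 17% missing, even the worst case keeps the sign of the point estimate. All of this assumes equal missing shares by arm and the design rates of 30% and 10% among those observed.

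**What to change.** In section {20c}, and in the analysis plan if it carries the same aim:

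1. Replace the aim of determining the mechanism with a statement that the primary analysis assumes missing at random given the model covariates.
2. Keep the review of levels and patterns, together with the recorded drop-out reasons, but only to describe missingness by arm and to choose auxiliary variables. Candidates already collected are baseline confidence in return to work, duration of unemployment, and work status at 3 and 6 months.
3. If any primary outcomes are missing after registry and self-report are combined, run two analyses whatever the pattern: multiple imputation under missing at random, and a departure analysis. The latter should count missing as not returned and also apply a delta shift, varied separately by arm, up to the point where the conclusion changes.

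The primary model stays as it is. The cost is a short paragraph and a few extra model runs, with no new data collection. If the analysis plan already contains step 3, only the protocol wording needs to change.

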### Plans to give access to the full protocol, participant-level data, and statistical code {31c}

Anonymised trial data and statistical analysis code may be accessed by contacting the corresponding author upon request. Deidentified data will be stored in the Norwegian Centre for Research Data repository to facilitate this.

### Oversight and monitoring

#### Composition of the coordinating centre and trial steering committee {5d}

The coordinating centre is located in Oslo at Kristiania University College, which is the trial sponsor. Research will be conducted within appropriate legal and ethical frameworks, supported by standard operating procedures and data management policies. The trial working group will meet weekly and consists of the chief investigator and three key members of the trial on-site at Kristiania University College. The trial management group includes all the collaborators and will regularly to oversee trial progress. The TSC will comprise seven members: the chief investigator, trial manager, four independent members recognised as experts in the field of vocational rehabilitation, and an additional user representative. The TSC charter may be requested by contacting the chief investigator. TSC meetings will follow DMC meetings and take place biannually to monitor study progress and provide public and/or professional advice, including review of project reports, protocols, amendments, and adherence to protocol. A user group will comprise six members, two of whom will join the trial management group. The composition of the user group will be a mix of people from the target population. The user group will provide advice from a user perspective and meet quarterly or depending on the need.

